## Statistical analysis

### Neuroimaging data analysis

Cerebral imaging testing will be entrusted to a third party, professionals of the independent neuroimaging research laboratory at Martinos Center for Biomedical Imaging, Massachusetts General Hospital, Harvard Medical School, USA, for statistical analysis. (1) fMRI data preprocessing: We will use SPM12 for slice timing correction (SPM12, http://www.fil.ion.ucl.ac.uk/spm/), rigid body correction for head motion with the FSL (https://fsl.fmrib.ox.ac.uk/fsl/fslwiki/) [33, 34], subjects with head movement < 1 mm and a rotational shift of < 2° will be entered into the subsequent analysis, bandpass temporal filtering (0.01–0.08 Hz), whole brain signal regression and ventricular and white matter signal regression. We will use the FreeSurfer version 6.0.0 software package to process the structural data and surface mesh representations of the cortex from each participant’s images [35]. Images will be reconstructed and registered to a common spherical coordinate system; functional images will be coregistered to anatomical images and normalized to the MNI152 standard template. (2) Morphological analysis of the grey matter structure of the brain: surface-based morphometry (SBM), voxel-based morphometry (VBM) and morphological analysis of subcortical grey matter structures in the grey matter of the brain will be based on anatomical data. The CIVET-pipeline toolkit and SurfStat software in the MATLAB environment will be used for the processing and statistical analysis of the image data. (3) Analysis of white matter parameters of the brain: Based on DTI scanning, the voxel-based analysis method will be used to process and analyse the test data using the MATLAB toolkit PANDA software. Image processing will include converting images from DICOM format to NIfTI format, eliminating extracerebral tissue and clip aligned images, eddy current correction and realignment, image normalization, calculating tensor and colour maps and fibre tracking and visualization. Finally, FSL software will be used to present the data, and the corresponding white matter fibre bundles will be identified according to the core white matter map of Johns Hopkins University. (4) Brain metabolite analysis: Based on the MRS scanning, images will be converted from DICOM format to RDA format, RDA data will be imported into the LC Model software, GAMMA software will be used in the same sequence and with the same parameters, the absolute concentration of each substance in the imported data will be calculated, and the substance concentration with SD < 15% will be imported into the SPSS 26.0 software package and analysed according to statistical principles. (5) Correlation analysis of SCV, CPT, McGill and multimodal brain imaging research data: Pearson linear correlation analysis in the SPSS 26.0 package will be used to correlate clinical effect indicators such as SCV, CPT and McGill values with the change values from multimodal brain images. The statistical threshold will be set as *P* < 0.05, a Pearson correlation coefficient of *r* > 0 will indicate a positive correlation, and *r* < 0 will indicate a negative correlation. According to the results of the correlation analysis, multiple regression analysis or principal component analysis will be carried out to deeply explore the brain function change characteristics and pathogenesis of brain central sensitization in PDPN.

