**Method and design:**

This will be a randomized controlled trial. A total of 150 participants will be recruited and assigned to one of three groups: the healthy group, the DM without PDPN group and the DM with PDPN group. Participants in the DM without PDPN and the DM with PDPN groups will each be further divided between an electroacupuncture group and a sham electroacupuncture group. Participants will receive six treatment sessions per week for 4 weeks. Multimodal cerebral imaging includes resting-state functional magnetic resonance imaging (rs-fMRI), diffusion tensor imaging (DTI) and magnetic resonance spectroscopy (MRS); this neurophysiological testing will be the primary outcome measure. Subjective pain scales and blood analysis will be a secondary outcome measure and will be used to assess the clinical efficacy of the intervention. Multimodal cerebral imaging will be used to detect cerebral activity changes in each treatment group. The clinical data and fMRI data will be analysed for all the groups. Multiple correlation regression analyses will be used to assess the association between changes in cerebral functional activity and the improvement of clinical outcomes after acupuncture treatment.

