#### Cerebral imaging index

The comprehensive application of multimodal cerebral imaging technology includes the use of rs-fMRI, MRS and DTI based on the BOLD effect. Based on the changes in the functional areas of the cerebral cortex, characteristics of functional connectivity in the whole cerebral cortex, functional connectivity between the cerebral cortex and subcortical nuclei and changes to the white matter and metabolic substances in the cerebral cortex, the objective is to analyse the functional and structural changes of cerebral central sensitization and its neuroimaging mechanism in participants with PDPN.

Based on the above results, participants with PDPN and non-PDPN will undergo multimodal cerebral imaging. The data for both groups will be compared and analysed for changes in cerebral functional areas, characteristics of whole cerebral functional connectivity, abnormal white matter and metabolic changes in the cerebral cortex. The aim of the analysis is to understand the mechanism of electroacupuncture in improving cerebral central sensitization in participants with PDPN.

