### Sample size calculation

This proposed study is an RCT whose primary aim is to evaluate the cerebral imaging mechanism of acupuncture to improve cerebral central sensitization and the clinical effect of acupuncture in patients with PDPN. Acupuncture is a complex intervention that differs from other treatments. Its therapeutic effect is changed if the acupoints are altered. No two-arm, randomized, sham-controlled trial has been conducted on this topic. For this reason, we are using our previous clinical experience to calculate the efficacy of electroacupuncture as an intervention [30, 31]. The proposed sample size of this trial was calculated mainly based on the Short-Form McGill Pain Questionnaire and the assumption that after treatment, the average change reported using this questionnaire would be greater for the experimental group than for the control group. The mean difference was 0.81, with a standard deviation of 0.07. Sample size was calculated using a noninferiority comparison. We set the alpha risk (*α*, type 1 error risk) at 0.025, the beta risk (*β*, type 2 error risk) at 0.2 and the critical value (*Δ*) at − 0.1. Calculating by using SAS [32], the sample size result was 24. Thus, according to this sample size calculation, each group should recruit 24 participants. Allowing for a 20% attrition rate in this study, we plan to recruit 150 participants, with 30 in each of the study groups. Healthy participants will not receive any treatment. Each participant will receive 2 rs-fMRI scans to observe different cerebral activities before and after acupuncture treatment.

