
### Clinical data analysis

According to the study data, the effect indices of the two groups will be calculated and compared to analyse the influence on the prognosis of PDPN. Indices of scales will be analysed by repeating measurement analysis of variance. The main analytical indicators will be the curative effect index and recurrence rate. A *t* test will be used for measurement data with a normal distribution. The Wilcoxon rank sum test will be used for nonnormal distribution; the Pearson chi-square test will be used for counting data. If it is a sequential concatenation table, the CMHX^2^ test will be used.

The measurement data of different treatment groups will be statistically described by the mean ± standard deviation (‾*χ* ± s). Intragroup differences will be assessed using a t-test at baseline; analysis of variance (ANOVA) will be used to compare measurement data at different stages; and SNK will be used for pairwise comparisons. Changes between groups before and after treatment will be analysed by ANOVA. If the data do not fit the above statistical analysis conditions (such as nonnormal), a nonparametric test will be used.

Counting data from different treatment groups are statistically described by frequency (constituent ratio). Changes between groups before and after treatment will be tested using the X2 test (CMHX2 test) or nonparametric test. The analysis of data results from participants not complying with the study protocol will be treated according to statistical analysis with randomization and multiple interpolation.

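### Keeping only metabolite concentrations with SD below 15% probably selects on the MRS outcome itself, shrinking differences for metabolites that are not well measured

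*Protocol article*

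**What the plan says.** The rule is in the protocol article, Statistical analysis, Neuroimaging data analysis, item (4). Spectra are converted and fitted ("RDA data will be imported into the LC Model software"), then "the absolute concentration of each substance in the imported data will be calculated", and finally "the substance concentration with SD < 15% will be imported into the SPSS 26.0 software package".

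The filtered values feed important analyses:

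- The abstract lists MRS with rs-fMRI and DTI and says that "this neurophysiological testing will be the primary outcome measure".
- The section Cerebral imaging index compares participants with and without PDPN on, among other things, "abnormal white matter and metabolic changes in the cerebral cortex".
- Item (5) of the neuroimaging analysis will "correlate clinical effect indicators such as SCV, CPT and McGill values with the change values from multimodal brain images".
- The planned size is 30 per group ("we plan to recruit 150 participants, with 30 in each of the study groups").

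The general scan quality control under Quality control and assurance does not alter which fitted values are kept. The only imputation mentioned is under Clinical data analysis: "The analysis of data results from participants not complying with the study protocol will be treated according to statistical analysis with randomization and multiple interpolation". It concerns participants who do not comply, not metabolite values that the filter removes.

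**The concern.** A precision cut-off looks like a neutral quality check. A percentage cut-off is not neutral when its denominator is the outcome. Two participants may have spectra of the same quality, and the one with less of the metabolite has the larger percentage error and is the one removed. If PDPN or treatment changes a metabolite, the group or visit with lower levels loses more values, and its remaining mean is pushed up further.

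Three results are at stake: the comparison of PDPN with non-PDPN participants, the EA-versus-sham comparison of change, and the correlations of change with SCV, CPT and McGill. A change value needs both visits to pass, so the losses compound. The article states the rule explicitly, so this is not a detail left for a separate analysis plan.

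**Working it through.** **Inputs from the article:** the cut-off of 15%, the absolute concentration as the analysed quantity, and 30 per group. The cut-off is a chosen threshold, so there is no calculated figure to reproduce.

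**Assumptions, not in the article:** SD in percent is s/c, where s is the absolute fitting error and c the estimated concentration. The filter acts on each value, with one value per person and visit. All means, spreads and error sizes below are assumed.

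**Step 1, algebra.** s/c < 0.15 is the same as c > s/0.15. For a given s, the rule truncates the outcome from below.

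**Step 2, closed form with equal absolute error.** The mean after truncation is μ + σ·φ(a)/(1 − Φ(a)), with a = (s/0.15 − μ)/σ. Take a control mean of 1, a lower-group mean of 0.80, σ = 0.15 and s = 0.12.

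- Cut-off: 0.12/0.15 = 0.80.
- Controls: a = (0.80 − 1)/0.15 = −1.33, and 91% are kept.
- Lower group: a = (0.80 − 0.80)/0.15 = 0, and 50% are kept.
- Remaining difference: 0.107 against a true 0.20, which is 54%.

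Over σ of 0.15 to 0.25 and true deficits of 0.10 to 0.20, the share of the difference that remains depends mainly on s:

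| s, as % of control mean | share of true difference remaining |
|---|---|
| 5% | 0.92–1.00 |
| 8% | 0.76–0.97 |
| 10% | 0.61–0.86 |
| 12% | 0.46–0.63 |
| 15% | 0.25–0.32 |

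**Step 3, simulation with error varying between spectra.** True means are 6.0 and 6.6 (difference 0.60), between-person SD is 1.0, and the log-scale SD of the error is 0.2. Typical absolute errors of 0.4, 0.6 and 0.8 are about 7%, 10% and 13% of 6.0. For the change comparison, the baseline mean is 6.0, the effect 0.60 and the SD of change 0.5, and both visits must pass.

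| typical error | cross-sectional difference | kept, lower / higher group | EA-minus-sham change |
|---|---|---|---|
| 7% | 0.59 | 99% / 100% | 0.595 |
| 10% | 0.52 | 91% / 95% | 0.56 |
| 13% | 0.43 | 65% / 77% | 0.51 |

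Relative to 0.60, the cross-sectional loss is about 13% at 10% error (0.08/0.60) and 28% at 13% error (0.17/0.60). The change comparison loses about 7% (0.04/0.60) and 15% (0.09/0.60).

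At 13% error, only 46% of one arm and 53% of the other keep a change value. Of 30 per arm, that is about 14 (0.46 × 30) and 16 (0.53 × 30).

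**Step 4, where the mechanism fails or reverses** (control mean 1, between-subject SD 0.20):

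- Error proportional to concentration, true deficit 0.15: almost no distortion (ratio 1.03).
- Higher group noisier (15% against 12%), true deficit 0.15: the difference grows (ratio 1.16).
- Lower group noisier (15% against 12%), true deficit 0.15: about 4% of the difference remains.
- Equal means, equal noise: no false difference.
- Equal means, noise 12% against 15%: a false difference of about 0.08.

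**The case against.** Several counter-arguments carry weight.

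- **Unit of the filter.** The sentence could mean that substances measured with SD below 15% go forward as a whole, which is close to the remedy proposed here. The section MRS scanning specifies multivoxel spectroscopy, so the voxel is a further possible unit. This stands as an ambiguity. The value-level reading is the natural one, and one sentence would settle it.
- **Meaning of SD.** The definition as relative fitting error is inferred from the percent sign and the fitting step. It is plausible, but it is an assumption.
- **Effect on inference.** The filter also narrows the spread, so standardised differences fall less than raw ones: from 0.51 to 0.48 at 10% error and from 0.46 to 0.40 at 13%. This stands, but it does not restore the lost participants.
- **Randomised comparison.** It suffers less than the cross-sectional one, as the last column of the table shows. With a constant shift and no variation in change, the figures are milder still: 0.573 at 10% and 0.528 at 13%. PDPN status is not randomised, so loss of the randomised sets concerns only EA versus sham.
- **Weight of MRS.** It is one of three imaging modalities. The Outcomes section also places SCV, CPT and McGill at the centre, and the sample size rests on McGill.

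A reader might infer that the rule biases metabolite results toward zero however well the spectra are acquired. The documents do not support that: they name no metabolites and give no precision, and at 7% error the difference is almost intact.

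**Conclusion.** The point holds in conditional form. If the rule is applied per value and SD is relative to the estimate, it selects on the outcome, and nothing else in the article offsets this. With similar absolute error in all groups, shrinkage is the expected direction: negligible near 5–7% error, material from about 10%. If error scales with concentration, the problem nearly disappears. If spectral quality differs between groups, the bias can go either way or create a difference where none exists.

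Two stronger conclusions should be avoided. Bias toward zero is not certain. Nor would larger losses at still higher error be recovered by the remedy below: at 17% error the simulated difference falls to about 0.38, but the pooled median relative SD is then about 15.9%, so a 15% rule per metabolite would drop that metabolite altogether.

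The rule should be changed, because the correction is cheap and protects against both bias and lost participants. It does not invalidate the imaging outcome as a whole.

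**What to change.** Reword item (4) of the neuroimaging analysis as follows.

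1. Define the SD and the unit to which it applies.
2. Apply the 15% criterion per metabolite: keep a metabolite if its median relative SD over all participants and both visits, pooled and blind to group, is below 15%. Then analyse every value of each metabolite kept.
3. Exclude individual spectra only on limits that do not depend on concentration, such as linewidth and signal-to-noise, or weight values by absolute fitting error.
4. Report exclusions by group and visit, with the value-level filter as a sensitivity analysis.

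The cost is analysis wording only; no new data are needed. The downside is that some noisier values stay in, which slightly widens intervals for less well-measured metabolites.

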## Outcomes

### Primary outcomes

The primary goal of this study is to observe the degree of peripheral neuropathy and measure the subjective pain perceptions in participants with PDPN before and after acupuncture treatment and assess their correlation with the characteristics of the central sensitization state of the brain. We will measure the sensory nerve conduction velocity (SCV) and the current perception threshold (CPT) and will use the McGill Pain Scale while also combining multimodal brain imaging data for our correlation analysis.

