#### Neurophysiological index

The SCV of the bilateral superficial peroneal nerve will be measured by EMG. CPT will be performed at 2000 Hz, 250 Hz and 5 Hz, and for each group, the CPT values on the dorsal side of the first bilateral toe will be measured. The Short-Form McGill Pain Scale will be used to evaluate the subjective pain experienced by the subjects in each group. Multiple regression analysis will be performed to analyse the correlation between the SCV, CPT, McGill Pain Scale values and the multimodal cerebral imaging results to reveal and verify the relationship between the degree of peripheral neuropathy, subjective pain and the changes in cerebral function in participants with PDPN.

Based on the above results, the SCV of the bilateral superficial peroneal nerve, the CPT value of the dorsal side of the first toe and the Short-Form McGill Pain Scale will be recorded and evaluated in participants with PDPN after each electroacupuncture and sham electroacupuncture treatment. We will continue to use the method of multiple regression analysis to analyse the correlation between the SCV, CPT, McGill Pain Scale values and the results of the multimodal cerebral imaging to study the relationship between the clinical therapeutic effect of electroacupuncture and the improvement of cerebral central sensitization and reveal the mechanism of electroacupuncture in the treatment of PDPN.

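### Clinical-by-imaging correlations that serve the primary goal are tested at a flat P < 0.05 with no multiplicity control stated, and their results steer the follow-up model on the same participants

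*Protocol article*

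**What the plan says.** Item (5) of the Neuroimaging data analysis section uses Pearson correlation in SPSS "to correlate clinical effect indicators such as SCV, CPT and McGill values with the change values from multimodal brain images". It sets one criterion: "The statistical threshold will be set as *P* < 0.05". No Bonferroni, false-discovery-rate, familywise or cluster correction is named for these tests or elsewhere in the imaging analysis. The only multiple-comparison procedure in the article is SNK, under Clinical data analysis, for pairwise clinical comparisons.

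The next step depends on the first: "According to the results of the correlation analysis, multiple regression analysis or principal component analysis will be carried out". No hold-out sample or cross-validation is described.

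The Primary outcomes section says that the trial will measure neuropathy and pain and "assess their correlation with the characteristics of the central sensitization state of the brain". The Neurophysiological index section gives the clinical readouts: "The SCV of the bilateral superficial peroneal nerve will be measured by EMG"; "CPT will be performed at 2000 Hz, 250 Hz and 5 Hz", on the first toe of both feet; and the Short-Form McGill scale. That section presents multiple regression as the means both to uncover and to confirm the link between neuropathy, pain and brain function.

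The Abstract states the intended analysis as one that will "assess the association between changes in cerebral functional activity and the improvement of clinical outcomes after acupuncture treatment".

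**The concern.** Many clinical readouts are crossed with many imaging measures, and each pair is judged against the same 5% criterion. Some pairs will pass by chance, and the number that do grows with the number of pairs. If the follow-up model is then shaped by which pairs passed, in the same people, it inherits those chance findings and cannot serve as a check on them.

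Because this analysis belongs to the primary goal, what is at stake is the trial's mechanistic conclusion: a reported link between symptoms and brain measures could arise with no link present.

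There is also a smaller wording problem. The Abstract speaks of brain change against clinical improvement, whereas the analysis section sets clinical values "with the change values from multimodal brain images".

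**Working it through.** The threshold is a design choice, so the plan has no figure of its own to reproduce.

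**Inputs from the protocol article**
- SCV: 2 values (bilateral nerve).
- CPT: 3 frequencies × 2 sides = 6 values.
- Imaging modalities: 3 (rs-fMRI, DTI, MRS). Grey-matter morphometry, item (2) of the imaging analysis, can be counted as a fourth family.
- Per-test threshold: 0.05.
- Participants: 30 per group, so 60 with PDPN if both arms are combined, or 60 × 0.8 = 48 after the planned 20% attrition.

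**Assumptions**
- McGill contributes one total score, which gives 2 + 6 + 1 = 9 clinical readouts.
- Each modality or family contributes one imaging feature. This is deliberately low, since the article lists whole-cortex connectivity, cortico-subcortical connectivity, white matter and metabolites.
- Ten features in total is shown as a higher case, and 3 measures × 3 modalities as a floor.

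**Formulas, with no true association and k tests**
- Expected false positives = 0.05 × k. Correlation among the tests does not change this.
- Chance of at least one, if independent = 1 − 0.95^k.

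| Tests | Expected false positives | At least one, independent |
|---|---|---|
| 3 × 3 = 9 | 0.45 | 37% |
| 9 × 3 = 27 | 1.35 | 75% |
| 9 × 4 = 36 | 1.8 | 84% |
| 9 × 10 = 90 | 4.5 | 99% |

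The expected count reaches 1 at 20 tests (20 × 0.05).

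**Allowing for correlation.** Two nerves and six toe readings from one person will not be independent. Null data were simulated at n = 30, 48 and 60, with equal correlation of 0.5 or 0.7 within the clinical set and within the imaging set. The chance of at least one false positive was:
- 9 tests: about 30% at correlation 0.5 and 22 to 23% at 0.7.
- 27 tests: about 57% and 39 to 40%.
- 36 tests: about 65% and 46%.
- 90 tests: about 88% and 65%.

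Sample size made little difference.

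**The follow-up model.** Suppose the imaging features that pass P < 0.05 against McGill are the ones entered in a regression on the same data. In null data with three imaging features, the overall F test was again significant in 88 to 100% of the datasets in which any feature passed. With a single selected feature the regression repeats the correlation test exactly. Such a model adds no independent confirmation.

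**The case against.** **The full statistical plan is not shown.** The Quality control section refers to one, and it could add a correction. That is true, and 'uncorrected' is not the article's word. But the article does not leave the threshold open: it states one, without qualification, for an analysis within the primary goal. An unseen plan would have to override it.

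**The number of tests is not fixed.** This stands. Under the 9-test floor fewer than one false positive is expected, and correlation among readouts lowers the chance of at least one. The size must be given as a range.

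**The regression may not be built from the significant pairs.** A reader might infer that only features passing P < 0.05 enter it. The text gives no such entry rule, offers PCA as an alternative and uses exploratory language; the Neurophysiological index section plans a regression without making it depend on the correlations. What is explicit is that the correlation results steer the follow-up. For the same reason, a very high false-positive rate for the regression, obtained by screening dozens of features against one score, should not be claimed. The documents give no such count. With four independent features the chance that any passes against one score is 1 − 0.95^4 = 19%.

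**Arm confounding.** A reader might infer that a shared treatment effect would masquerade as mechanism. That requires the electroacupuncture and sham arms to be pooled, which the text does not state.

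**Change and population.** A reader might infer that raw clinical values will be correlated with imaging change. Given the Abstract, this is better read as loose wording to be aligned. Nor is the population clearly wrong: the regressions are already described for participants with PDPN.

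**Weight of the analysis.** The correlation is part of the primary goal, not all of it, and the sample size rests on McGill. This limits the consequence but does not remove it.

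**Conclusion.** The point holds as a multiplicity and selection problem in a stated rule. A flat 5% threshold over a clinical-by-imaging grid gives 1.35 to 1.8 expected false positives at 27 to 36 tests when nothing is there. The chance of at least one is 75 to 84% under independence and roughly 40 to 65% with correlation of 0.5 to 0.7 within both sets. These figures rest on one McGill total and one imaging feature per modality or family. At 9 tests they fall to 0.45 and 37%, and with more imaging features they rise. Follow-up modelling steered by those results on the same participants cannot confirm them. The documents do not establish that arms will be pooled or that only the significant pairs will be modelled.

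**What to change.** - Replace the flat P < 0.05 in item (5) with control of the false discovery rate at 5% across a declared family of clinical-by-imaging tests, listing the clinical readouts and imaging features that make it up.
- State that clinical change is correlated with imaging change, in line with the Abstract, and adjust for arm if the arms are combined.
- Name the regression variables in advance, or label any regression or PCA guided by the correlation results as exploratory, and do not present it as verification.
- Align the Neurophysiological index section with item (5), so that it is clear whether the regression depends on the correlations.

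The cost is wording, minor analysis work and fewer nominally significant correlations. As a guide to the strict end, Bonferroni over 27 tests uses 0.05/27 = 0.00185 per test. The correlation needed rises from 0.254 to 0.394 at n = 60, and from 0.361 to 0.545 at n = 30. False-discovery-rate control is no stricter than this and is more lenient when several associations are real. Trial conduct does not change.
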